## Abstract

**Introduction:**

Catheter-related sepsis is one of the most dangerous complications of neonatal intensive care and is associated with significant morbidity and mortality. Use of catheter-care ‘bundles’ has reduced the incidence of catheter-related sepsis, although individual components have not been well studied. Better evidence is needed to guide selection of the most appropriate antiseptic solution for skin disinfection in preterm neonates. This study will inform the feasibility and design of the first randomised controlled trial to examine the safety and efficacy of alcohol-based versus aqueous-based chlorhexidine antiseptic formulations for skin disinfection prior to percutaneous central venous catheterisation in preterm neonates. The antiseptics to be compared are 2% chlorhexidine gluconate (CHG) aqueous and 2% CHG in 70% isopropyl alcohol.

**Methods and analysis:**

The Antiseptic Randomised Controlled Trial for Insertion of Catheters (ARCTIC) is a two-centre randomised-controlled feasibility trial. At least 100 preterm infants born at <34 weeks’ gestation and due to undergo percutaneous insertion of a central venous catheter will be randomly allocated to receive prior skin disinfection with one of the two antiseptic solutions. Outcomes include: i) recruitment and retention rates; ii) completeness of data collection; iii) numbers of enrolled infants meeting case definitions for definite catheter-related sepsis, catheter-associated sepsis and catheter colonisation and iv) safety outcomes of skin morbidity scores recorded daily from catheter insertion until 48 hours post removal. The key feasibility metrics will be reported as proportions with 95% CIs. Estimated prevalence of catheter colonisation will allow calculation of sample size for the large-scale trial. The data will inform whether it will be feasible to progress to a large-scale trial.

**Ethics and dissemination:**

ARCTIC has been approved by the National Health Service Health Research Authority National Research Ethics Service Committee East of England (Cambridge South) (IRAS ID 163868), was adopted onto the National Institute of Health Research Clinical Research Network portfolio (CPMS ID 19899) and is registered with an International Standard Randomised Control Trials Number (ISRCTN82571474; Pre-results) and European Clinical Trials Database number 2015-000874-36. Dissemination plans include presentations at scientific conferences, scientific publications and sharing of the findings with parents via the support of Bliss baby charity.

**Trial registration number:**

ISRCTN82571474; Pre-results.

Strengths and limitations of this studyThe Antiseptic Randomised Controlled Trial for Insertion of Catheters study will be one of only very few randomised controlled trials of skin antiseptics in preterm neonates and the first to compare aqueous 2% chlorhexidine gluconate versus 70% isopropyl alcohol-based 2% chlorhexidine gluconate for cutaneous disinfection prior to central venous catheterisation.The trial will collect rigorous, prospective safety data following antiseptic application through daily skin safety assessments using a validated neonatal skin scoring tool.This will be the first study in neonates to undertake molecular typing of isolates to verify that skin-colonising and blood-cultured organisms match catheter-colonising organisms to a species level in babies with suspected sepsis, thus allowing definitive proof of catheter-related sepsis.Catheter colonisation will be used as a proxy for catheter sepsis, and the target sample size is based on an anticipated incidence of catheter colonisation of 20% in the reference antiseptic group, estimated with a 95% CI of 11% to 31%; the study is not powered to detect differences in clinical outcomes.This trial will show whether a future large-scale multicentre randomised controlled non-inferiority trial of the same antiseptics is feasible and will determine the sample size required for such a trial.

## Introduction

Percutaneously inserted central venous catheters (PCVCs) are inserted daily in neonatal intensive care units (NICUs) across the world to deliver hyperosmolar parenteral nutrition solutions to preterm neonates. PCVCs may remain in situ for weeks,^1^ but their presence entails a major risk for bloodstream infection. In a previous study, 32% of inserted PCVCs were colonised with potentially pathogenic bacteria at the point of removal, and 8% overall were associated with definite catheter-related sepsis (CRS).^1^ Extraluminal colonisation is the main route of catheter colonisation in short-term CVCs: skin bacteria traverse the catheter insertion site onto the catheter, colonise the line and act as focus for CRS.^2^ In one study, the presence of skin bacteria at the catheter exit site was associated with an 8-fold increased risk of catheter colonisation and a 10-fold increased risk of CRS caused by the same organism.^2^

For preterm babies in the NICU, CRS is a dangerous complication associated with significant morbidity and mortality. Sepsis increases the duration of intensive care and hospitalisation, need for antibiotics and risks for adverse neurodevelopmental outcome. Coagulase-negative staphylococcal infections cause the majority of CRS in the NICU (80%–90%), may be life-threatening and can cause permanent lifelong injury and disability in survivors, including cerebral palsy.^3 4^

Reduction of CRS has been a major goal of the National Health Service for the past decade.^5^ Catheter-care ‘bundles’, guidelines incorporating collected good practices for catheter insertion and maintenance, have successfully reduced the incidence of catheter colonisation and CRS in the NICU,^6^ although await universal adoption.^7^

The individual components of catheter-care bundles have not been well studied in randomised controlled trials (RCTs). Adequate skin disinfection of the catheter insertion site is arguably the most important component of catheter-care bundles to prevent catheter colonisation and CRS. Optimal skin preparation will abolish or significantly reduce numbers of skin organisms, so limiting risks of residual skin colonisation by bacteria that may then colonise a PCVC and cause CRS.

Studies in adults, including meta-analysis, show that alcohol-based antiseptics are superior for topical antisepsis,^8 9^ and UK national evidence-based guidelines recommend use of 2% chlorhexidine gluconate in 70% isopropyl alcohol (2%CHG-70%IPA) for skin antisepsis in adults and older children. However, there is no guidance for preferred antiseptic in infants, including preterm infants, due to the lack of evidence and specific safety concerns in this population.^10 11^ The best antiseptic to use for preterm babies is still unknown, and multiple different antiseptics, combinations and concentrations are presently being used in UK NICUs; approximately half use a 2% concentration of CHG and 60% an IPA-containing CHG formulation.^12^ For preterm neonates, there is no Cochrane review comparing skin antiseptics for cutaneous disinfection prior to PCVC insertion, and only two RCTs have compared topical antiseptics for PCVC insertion.^13 14^

There are risks associated with antiseptic use peculiar to preterm infants. Their thin skin is vulnerable to chemical injury and absorption. Chemical skin burns have been described with all the currently used topical antiseptics, including both aqueous and alcohol-containing CHG formulations, and iodine solutions,^15^ as well as with octenidine.^16^ Topical alcohol use may also increase the risk of systemic chemical absorption.^17^

There are no published RCTs that have examined the safety and efficacy of alcohol-based versus aqueous CHG formulations for neonatal antisepsis. This feasibility study aims to inform the safety and assist the design and planning of a future large-scale multicentre RCT that will examine whether 2% CHG aqueous is non-inferior in antiseptic efficacy compared with 2%CHG-70%IPA for skin disinfection prior to PCVC insertion in preterm neonates. An aqueous CHG is likely to have fewer side effects than an alcohol-based CHG, and would therefore be preferable if found to be non-inferior in terms of antisepsis.

## Objectives

To determine the proportion of babies in the 2%CHG-70%IPA group with colonisation of at least one of the two catheter segments taken at catheter removal. Catheter colonisation will be the primary outcome in the full-scale trial because it is a valid surrogate for CRS^2^; to determine factors affecting recruitment and process outcomes that will help refine the design of the large-scale trial; also to estimate numbers of enrolled infants who have definite CRS and numbers with catheter-associated sepsis, determine suitability and completeness of data collection methods and describe any skin morbidity occurring in trial participants related to use of the study antiseptics.

## Methods and analysis

### Study design

A feasibility, masked RCT of Investigational Medicinal Products (IMPs). Preterm infants born at <34 weeks’ gestation who are due to undergo planned insertion of a PCVC will be randomised to receive one of two topical disinfection agents for skin antisepsis: 2% chlorhexidine gluconate aqueous (2%CHG-aqueous) or 2%CHG-70%IPA.

#### Study setting

Two tertiary-level neonatal units in the UK, Norfolk and Norwich University Hospital and Medway Maritime Hospital, which each cater to a total of 5000–6000 deliveries per year.

## Eligibility

### Inclusion criteria

Preterm infants born at <34 weeks’ gestation.Requiring routine insertion of a PCVC for parenteral nutrition.No new episode of suspected sepsis with commencement of antibiotics occurring within the 48 hours preceding planned catheter insertion.No other indwelling PCVC already in situ.

### Exclusion criteria

No realistic prospect of survival in the short term.Life-threatening congenital abnormality.Underlying skin condition.Another indwelling PCVC already in situ or previously enrolled into the study.Positive blood culture (BC) within the past 7 days without a subsequent negative BC result.Antibiotic treatment commenced for suspected sepsis within the preceding 48 hours.

### Key definitions

*Definite* CRS: a peripheral BC plus any catheter segment (ie, one of the ~1 cm long proximal or tip catheter portions) positive with the same organism, based on bacterial culture, antibiotic sensitivity and molecular typing, from a neonate who had an indwelling PCVC and clinical signs of sepsis but no other focus of sepsis.

*Catheter colonisation*: a catheter that at the time of removal has either one or both segments that are culture positive.

*Catheter-associated sepsis*: a baby with clinical signs of sepsis and an accompanying positive BC in the period between catheter insertion and 48 hours post removal but who has no other focus of sepsis and in whom both catheter segment cultures are negative.

### Recruitment

Preterm babies potentially suitable for the trial will be identified by the clinical healthcare teams. Parents of such infants will be approached for consent by the research team or delegated suitably qualified member of the clinical healthcare team trained in study procedures and Good Clinical Practice (GCP). A written parent information sheet that forms part of the Parental Informed Consent Form will be provided to help explain the study (online supplementary file 1). Written maternal consent will be obtained and countersigned by the person who obtained informed consent (principal investigator (PI), or appropriately qualified healthcare professional with delegated authority).

10.1136/bmjopen-2018-028022.supp1Supplementary file 1

### Randomisation

Following consent, randomisation to either 2%CHG-70%IPA antiseptic or 2%CHG-aqeuous antiseptic will take place as close as possible to the time of planned catheter insertion. Randomisation will be managed via a secure web-based facility hosted by the National Perinatal Epidemiology Unit Clinical Trials Unit (CTU) and will use a 3:1 allocation ratio in favour of the 2%CHG-70%IPA antiseptic group, the group that will inform the power calculation for the large-scale trial. Groups will be stratified by birth gestation (<28 weeks; 28 weeks+0 days to 33 weeks+6 days) and by centre. Treatment allocation will be masked such that the allocation will not be known by clinicians, the baby’s family, laboratory staff or trial outcome assessors.

### Interventions

The trial procedures are summarised in figure 1.

**Figure 1 F1:**
[figure not shown]
Trial procedures.

### Skin disinfection at catheter insertion

Study packs stored in a locked, secure, temperature-monitored cupboard will contain two bottles of the same allocated antiseptic Investigational Medicinal Product (IMP) each labelled with the same identifying code. One bottle will be opened at catheter insertion, the other will be retained for use at catheter removal. The disinfection procedure requires sparing application of allocated antiseptic solution for 10–20 s from sterile gauze to the skin site area selected for catheterisation. Instructions are: use only the minimal volume of antiseptic necessary for skin coverage, avoid any pooling of antiseptic, ensure that any excess solution and any soaked drapes or gowns are removed to avoid any prolonged contact with the skin and allow the disinfected area to air dry completely (for ≥30 s) before proceeding with catheter insertion. Excepting in the case of failed catheterisation, saline or water must not be used to wipe the disinfected skin area following application of antiseptic solution.

### Catheter insertion

Catheter insertion will be standardised, using a working guideline common to both participating centres that requires strict aseptic technique and encompasses established good clinical practices for PCVC insertion and care adopted from catheter-care bundles^6 8 18 19^ The decision to insert a PCVC and choice of catheter (Premicath 1Fr/28G or Epicutaneo-Cava catheter 2Fr/24G: both Vygon (UK), Cirencester, UK) is at the discretion of the attending clinical team. All personnel involved will be trained in catheter insertion and maintenance procedures. An insertion checklist will be completed for all catheterisations and a disposable face mask will be worn by the operator inserting the catheter for asepsis purposes and also to minimise the risk of possible unblinding from any smell of alcohol.

### Assessment of skin condition

Skin status will be recorded using a validated neonatal contact dermatitis scoring system, the Neonatal Skin Condition Score,^20^ with minor modification. Assessments will be undertaken by a nurse trained in use of the scoring system and will be recorded at baseline (prior to application of antiseptic), within 10–30 min after catheter insertion and then daily until 48 hours following catheter removal, or daily for 48 hours after antiseptic application in cases where catheterisation is unsuccessful. Serious chemical skin burns adjudged by a PI or delegate to be severe or moderately severe, will be notified to the Medicines and Healthcare Products Regulatory Agency (MHRA).^21^

### Catheter removal and obtainment of study specimens

Catheters are usually removed when no longer required, although sometimes removal is warranted earlier than intended because of complications, including suspected sepsis. If a catheter is being removed from a baby with suspected sepsis then a concurrent peripheral BC will be obtained as per routine clinical practice. The decision for catheter removal for enrolled babies lies with the attendant clinical team.

The following samples will be obtained at the time of catheter removal for microbiological analysis:Two exit site skin swabs taken *before* catheter removal: the first after removing all covering dressings but prior to skin disinfection; the second taken post new disinfection of the insertion site, once the antiseptic has dried. This disinfection procedure is intended to limit the risk of catheter contamination by residual skin organisms during the removal of the catheter and will use the same allocated antiseptic as was used for catheter insertion. Both specimens will be obtained by rolling the swab tip several times across the skin of the catheter insertion site, over an area within <0.5 cm radius of the insertion site and including the actual puncture site.Two approximately 1 cm long catheter segments (proximal and tip) *after* catheter removal. Proximal catheter segments have higher colonisation rates than tips,^1^ therefore microbiological analysis of both catheter segments rather than the tip alone may improve the diagnostic yield of catheter colonisation.

Catheter removal requires two trained persons and care to avoid cross-contamination between segments while sectioning the catheter. Two separate sets of sterile forceps, two pairs of sterile scissors and two sterile prelabelled universal containers are required. Before removing the catheter, the subcutaneous insertion length will be noted from the external catheter markings. The catheter will be removed onto a sterile paper towel field then sectioned using separate pairs of sterile scissors to obtain two ~1 cm long formerly subcutaneous catheter segments: i) tip and ii) a proximal segment, taken approximately 1–2 cm distal to the point of skin entry (figure 2). The individual segments will be placed into separate appropriately labelled sterile universal containers using separate pairs of sterile forceps.

**Figure 2 F2:**
[figure not shown]
Picture showing catheter sections taken at catheter removal.

### Microbiology

The catheter segments and skin swabs will be submitted to the local microbiology laboratories for routine culture and antibiotic sensitivities. BCs sent from babies with suspected sepsis at the time of catheter removal will undergo standard culture methods. Bacterial growths from skin swab cultures will be assessed using a semi-quantitative method.^22^ All laboratory staff will be blinded to antiseptic allocation. Isolates from culture-positive skin swabs, blood and catheter segmental cultures will be retained for molecular typing. Initial identification of organisms will be done by mass spectrometry. Those giving similar patterns will be analysed using next-generation sequencing using a multiplexed approach on the Illumina MiSeq. Molecular typing of paired blood and catheter isolates from the same baby will allow confirmation that isolates are identical to a species level, for definitive diagnosis of definite CRS. While few postdisinfection skin swabs are expected to be positive, molecular typing of skin swab isolates will be done for any babies with colonised catheters: isolation of paired identical species could indicate possible catheter contamination by skin organisms during catheter removal. Babies with positive BCs will be managed according to local clinical guidelines; involvement in this trial will not dictate or influence clinical antibiotic prescriptions.

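### A species-level match between blood and catheter isolates is called definitive for definite CRS, but it cannot exclude unrelated strains of the same skin species

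*Protocol article*

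**What the plan says.** Three places in the protocol article bear on this.

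- **Key definitions.** Definite CRS needs a peripheral blood culture and a catheter segment "positive with the same organism, based on bacterial culture, antibiotic sensitivity and molecular typing". The baby must also have had a catheter in place and shown clinical sepsis without an alternative source of infection. The level at which typing must agree is not given here.
- **Microbiology.** The first step is stated as "Initial identification of organisms will be done by mass spectrometry". Then: "Those giving similar patterns will be analysed using next-generation sequencing". The use made of the result for blood and catheter pairs is that it "will allow confirmation that isolates are identical to a species level, for definitive diagnosis of definite CRS".
- **Strengths and limitations box.** Organisms will be shown to "match catheter-colonising organisms to a species level in babies with suspected sepsis, thus allowing definitive proof of catheter-related sepsis".

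So the level of agreement appears only in the second and third places. Both times it is species, and both times it is presented as settling the diagnosis. The article names no strain-level or clonal criterion.

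**The concern.** The Introduction says that coagulase-negative staphylococci cause most CRS on neonatal units, and that catheters are colonised mainly by skin bacteria tracking in from the insertion site. A skin organism can also reach a blood culture from the sampling site. A baby with a colonised catheter and a contaminated blood culture may therefore yield the same species twice from two unrelated strains. Agreement on species is what one would see in true CRS, but it is also what one may see without it.

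The laboratory sequence sharpens the point. Isolates reach sequencing only if their mass-spectrometry patterns are already similar. If sequencing is then read only to species level, it adds little to the first identification.

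Two listed outcomes are at stake: the proportion of infants meeting the definite CRS definition, and the CRS rate per 1000 catheter days. Few events are expected, so a single misclassified baby would be visible in either.

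**Working it through.** **1. The plan's own figures.** Sample size gives 20% of n=70 with a 95% CI of 11% to 31%. The exact interval for 14/70 is 11.4% to 31.3%, so this reproduces. It rests on segment culture alone. Nothing in the sample size uses typing.

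**2. Expected CRS cases.** The Introduction gives definite CRS in 8% of catheters in the previous study. Sample size gives 93 babies and a 34% lower CRS rate with the alcohol-based product (4.5/6.8 = 0.66).
- At the previous proportion: 93 × 0.08 = 7.4.
- With the reduction: 7.4 × 0.66 = 4.9.

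The expected number is about 5 to 7. One extra case would raise it by 1/7.4 = 13% to 1/4.9 = 20%.

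**3. Probability that an unrelated pair matches (illustration).** The article gives no species mix, antibiogram diversity or blood-culture contamination rate, so the inputs below are assumptions except where noted.
- c = probability that an isolate is a coagulase-negative staphylococcus: 0.8 to 0.9. This borrows the Introduction's share of CRS and applies it to each isolate.
- f = share of the commonest species within that group: 0.4 to 0.8, with the rest split evenly over four species.
- s = probability that two unrelated isolates in the group share a species = f² + 4 × ((1 − f)/4)². For f = 0.4, s = 0.16 + 0.09 = 0.25. For f = 0.8, s = 0.64 + 0.01 = 0.65.
- a = probability that the antibiograms of such a pair agree: 0.25 to 1.

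Species alone, c² × s:
- low: 0.64 × 0.25 = 0.16
- high: 0.81 × 0.65 = 0.53

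With antibiotic sensitivity added, as the case definition requires, c² × s × a:
- low: 0.16 × 0.25 = 0.04
- high: 0.53 × 1 = 0.53

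**4. Expected false definite CRS cases.** Apply 20% colonisation to all 93 babies (the plan anticipates it for the reference arm only): 93 × 0.20 = 18.6 colonised catheters. Let b be the share of these babies who also have an unrelated positive blood culture and meet the clinical criteria. Assume b = 0.05 to 0.20.
- low: 18.6 × 0.05 × 0.04 = 0.04
- high: 18.6 × 0.20 × 0.53 = 2.0

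The range runs from practically none to about two, and its width comes from inputs that the article does not supply.

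**5. Consistency within the Microbiology section.** For skin and catheter pairs, the section says only that identical species might point to possible contamination at removal. For blood and catheter pairs, identical species is treated as conclusive. Part of that caution may concern when the contamination occurred, so the contrast is suggestive rather than decisive. It does show that the section does not treat species identity as conclusive everywhere.

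**The case against.** The strongest reply is that the outcome is counted by the case definition in Key definitions, where species identity is not the only test. Matching antibiotic sensitivity discriminates within a species, and clinical signs with no other focus remove some contaminated cultures. This stands in part: it rules out the reading that species identity alone decides the case. It does not remove the problem. Unrelated strains can share an antibiogram, and the clinical criteria describe the baby rather than the source of the blood isolate. The remaining element, typing, is the one that Microbiology sets at species level.

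A second reply is that the article condenses a full protocol, and that relatedness thresholds belong there or in the analysis plan. That is fair as to the threshold, whose absence is not criticised here. The point concerns what the article does state: a level of match, and a claim for it that the level cannot carry.

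Third, a reader might infer that the plan throws away its sequencing data. The article does not say so. It says what typing will allow, and the type of sequencing is described only as multiplexed, so its resolution is unknown.

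A reader might also infer that false matches weaken the case for colonisation as the large trial's primary outcome. The documents do not support this. Objectives rests the surrogate on a cited study, and the listed outcomes include no analysis of the association between colonisation and CRS. By definition every definite CRS case has a positive segment, whichever typing level is used.

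**Conclusion.** The point holds in a limited form. The article calls a species-level match definitive, and with the organisms that it expects, such a match is not. Some chance matches can be counted as definite CRS.

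It would be tempting to say that they will be counted, or that the CRS rate is inflated by a stated percentage. Neither follows. The illustration gives about 0.04 to 2 false cases against about 5 to 7 expected. Both ends depend on an assumed species mix, antibiogram agreement and frequency of unrelated positive cultures, so the true number may be zero.

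Only the definite CRS proportion and the CRS rate per 1000 catheter days are affected. The primary outcome is segment culture without typing, and the sample size does not depend on CRS classification. The article also says that the study is not powered for clinical outcomes. The point merits correction because two reported outcomes and a headline strength rest on the wording and the change is small.

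**What to change.** Bring the strengths and limitations box and Microbiology into line with Key definitions.

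1. State, before unmasking, that the typing element of the same-organism requirement is strain-level relatedness from the sequencing already planned, with a fixed threshold. Keep the antibiotic-sensitivity and clinical elements as they are.
2. Report species-level concordance as a sensitivity classification, so that the CRS proportion and rate appear under both rules.
3. Report species-matched but strain-discordant babies as a separate category. They would leave definite CRS but could not enter catheter-associated sepsis, which requires both segments to be negative, so they would otherwise be lost from the tables.
4. If the planned sequencing cannot resolve strains, remove the claims of definitive proof and definitive diagnosis from both places and describe the result as species-level concordance.

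The cost is a change of wording and some bioinformatic work. Isolates are already to be retained and sequencing is already planned, but the cost would be higher if the present method does not give strain resolution. The reported CRS rate may come out lower.
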